## Abstract

**Background:**

A drug-repurposing-specific phenome-wide association study (PheWAS) demonstrated that patients with a single nucleotide variant that decreases expression of platelet-derived growth factor receptor beta (PDGFRβ) have a higher prevalence of fistulas, suggesting that PDGFRβ signaling is important for tissue repair. Recombinant human platelet derived growth factor B (rhPDGF) is an FDA-approved protein-based therapeutic that signals through PDGFRβ to heal and regenerate cutaneous skin wounds, periodontal tissue, and orthopedic bone with a strong safety profile. We hypothesize that rhPDGF will benefit other conditions identified by PheWAS with a similar physiological mechanism as the existing indications, such as complex perianal fistulas that are ineligible for a fistulotomy.

**Methods and analysis:**

This prospective, blinded, single-site study aims to enroll 12 participants, randomized at a ratio of 2:1, comparing implantation of rhPDGF-enhanced collagen to routine care procedures, and stratified by fistula etiology, idiopathic versus Crohn’s disease (CD)-related. The primary outcome of this study will evaluate the technical performance of the rhPDGF-enhanced collagen implant for treatment of complex perianal fistulas as measured by the proportion of participants with successful implantation of the intervention without any intervention-related serious adverse events. The secondary outcomes will assess the preliminary safety and efficacy of the intervention based on all intervention-related adverse events, total fistulas healed, rate of fistula recurrence, and change in patient-reported symptoms. Complex perianal fistulas, idiopathic or CD-related, remain a major clinical challenge in need of new multimodal treatments aimed at tissue repair and regeneration. Pharmaceutical rhPDGF stimulation of PDGFRβ signaling promotes healing of skin, bone, and soft tissue. PheWAS revealed fistulas as a novel indication for repurposing rhPDGF. This protocol aims to evaluate the technical performance, preliminary safety and efficacy, and feasibility of rhPDGF-enhanced collagen for healing and remission of complex perianal fistulas.

**Ethics and dissemination:**

This trial was approved by the Vanderbilt University Medical Center institutional review board (IRB#240585). Results will be submitted for publication in a peer-reviewed journal.

**Clinical trial registration:**

This trial is registered at ClinicalTrials.gov (NCT06632418).

## INTRODUCTION

Repurposing drugs with existing safety data has many advantages in clinical trials but involves the identification of a novel and precise indication where the drug can address an unmet medical need effectively. Vanderbilt University Medical Center’s (VUMC) academic drug repurposing program leverages human genetic variation to inform drug repurposing and bypass the limitations of *in vitro* and preclinical models. Phenome-wide association studies (PheWAS) using deidentified patient DNA samples, single nucleotide variant (SNV) genotyping data, and electronic health records can identify and validate associations between SNVs that cause specific protein changes that correlate with a drug’s effects and novel disease phenotypes that are potentially treatable by the drug (1–3). A PheWAS analysis performed by our team linked a SNV in the platelet-derived growth receptor beta gene (*PDGFRB*), that decreases PDGFRβ protein expression, with *increased* prevalence of chronic wounds, tissue defects, and higher rates of graft, reconstructive, and transplant procedures in patients carrying at least one copy of the variant allele. This suggests that the PDGFRβ signaling pathway is critical during wound healing and tissue regeneration following tissue injury or damage and that stimulation of this pathway may accelerate healing and promote repair (4).

PDGFRβ is one of two isoforms of the tyrosine kinase receptors that bind the PDGF family of growth factors found naturally in the body. PDGF-BB homodimers bind to PDGFRβ and promote chemotaxis, mitogenesis, and survival of many different cell types and extracellular matrix deposition during embryonic development and tissue repair following injury. Recombinant human PDGF-BB (rhPDGF) is a pharmaceutical recombinant protein therapy that mimics the activity of the endogenous growth factor that is FDA-approved for the treatment of diabetic foot ulcers (DFU), periodontal bone and soft tissue reconstruction, and orthopedic bone regeneration, and has over 150 published clinical studies demonstrating its safety. Our PheWAS analysis showed an increased prevalence of DFUs, periodontitis, and orthopedic bone disorders associated with the PDGFRβ SNV. The presence of these existing indications in the dataset validated the biological consequences of the SNV and supported the selection of a novel phenotype from the PheWAS. Furthermore, the analysis revealed an increased prevalence of fistula occurrence associated with the PDGFRβ SNV, revealing a novel indication for repurposing rhPDGF.

Perianal fistula, an abnormal connection between the rectum and perianal epithelium, is a common cause of anorectal burden with an overall incidence of 9 cases per 100,000 (5). Anal fistulas account for up to 5% of proctological consultations and are often responsible for substantial detriment to patient quality of life in terms of pain, fecal incontinence, and psychologic distress (6). The generally accepted pathophysiology of idiopathic, or cryptoglandular, fistulas, accounting for 90% of all cases, includes obstruction of an anal gland followed by chronic infection and epithelization of the abscess drainage tract (7,8). However, mechanistic clarity regarding proposed pro-inflammatory and infectious factors remains elusive (9–12). The second most common cause of perianal fistulas is due to Crohn’s disease (CD), a chronic inflammatory disease of the gastrointestinal tract with an estimated annual incidence of 3 to 20 cases per 100,000 (13). Approximately 20% of patients with CD will develop a perianal fistula within 10 years of diagnosis (14) as a severe complication of chronic intestinal inflammation, extracellular matrix remodeling, and pathogen-associated molecular patterns resulting in epithelial-to-mesenchymal transition and tissue remodeling mechanisms that pave the fistula tract (15).

Idiopathic perianal fistulas are primarily treated with surgical interventions after seton placement which allows the abscess to drain and clears the infection. CD-related perianal fistulas rely on a combination of pharmacological therapies to reduce chronic inflammation and control infection in addition to seton placement, and definitive surgical procedures are only considered once inflammation is controlled. The optimal treatment strategy and prognosis depend on the fistula classification as simple or complex as defined by the anatomy, single tract or branching, and the proportion of the sphincter muscle that is involved (16). For patients with preoperative fecal continence and simple fistulas with minimal sphincteric involvement, fistulotomy, a procedure wherein the physician cuts open the length of the fistula, is often an effective treatment resulting in healing for over 90% of patients (17). Options for complex fistulas involving more of the sphincter muscle are broad and must be carefully selected to minimize the risk of long-term incontinence. Fistulotomy, fistulectomy, ligation of the intersphincteric fistula tract (LIFT), endorectal advancement flap, modified Hanley procedure, anal fistula plug implantation, or natural healing are the standard treatment choices with variable success rates between 15.8–72.7% for complete healing, likelihood of recurrence, and risk of long-term bowel incontinence (18,19).

Non-invasive, pharmacological, medical options are lacking for perianal fistulas (11,20). Recent investigations have focused on targeting the processes of collagen remodeling and epithelial to mesenchymal transformation to promote natural healing with mixed evidence regarding the effectiveness of implantable bioprosthetic collagen plug, acellular crosslinked collagen matrix, and fibrin glue scaffolds (8,21). Although these minimally invasive therapies lack clear superiority over traditional surgical techniques, the dearth of less invasive options and need for sphincter-sparing modalities justifies the continued search for and optimization of therapies that target the underlying mechanistic drivers of perianal fistula formation, persistence, and recurrence.

Increased prevalence of a fistula diagnosis was found in the PDGFRβ PheWAS dataset. As such, we hypothesized that targeting the PDGFRβ signaling pathway by delivery of rhPDGF will promote repair and prevent recurrence of complex perianal fistulas. Systematic review of the literature revealed that blood-derived products, concentrated with PDGF-BB, improved healing rates of various fistula types in preclinical and clinical studies (22–28), further supporting that targeting this biological mechanism may benefit complex perianal fistula treatment outcomes, addressing a major unmet need in the clinic. We propose that rhPDGF will enhance healing of perianal fistulas by stimulating chemotaxis and mitogenesis of the cell types that deposit connective tissue, form new blood vessels, and regrow damaged tissue. This clinical trial aims to evaluate rhPDGF as an adjunct therapy to the implantation of a collagen matrix for treatment of complex perianal fistulas not amenable to fistulotomy.

## METHODS

### Trial design

This study will be carried out in accordance with International Conference on Harmonisation Good Clinical Practice (ICH GCP) and the United States (US) Code of Federal Regulations (CFR) applicable to clinical studies (45 CFR Part 46, 21 CFR Part 50, 21 CFR Part 56, 21 CFR Part 312, and/or 21 CFR Part 812). This Phase II clinical trial will evaluate the performance, preliminary safety and efficacy, and feasibility of rhPDGF-enhanced collagen on healing complex perianal fistulas that are not eligible for a fistulotomy in patients 21 years of age and older. This prospective, blinded, single-site study is expected to enroll and randomize 12 participants at a 2:1 intervention versus control allocation ratio stratified by fistula etiology, idiopathic versus CD-related. The two arms will compare implantation of the rhPDGF-enhanced collagen to routine care procedures, which include COOK Biotech’s Biodesign^®^ Anal Fistula Plug implant for idiopathic fistulas or draining seton removal and natural healing for CD-related fistulas. Following the baseline procedure, patients will be evaluated at Months 1, 3, and 6 to assess healing of the external fistula opening and change in pain, incontinence, and other perianal fistula-related symptoms. Patients randomized to the control group who fail to heal at Month 3 will have the option to crossover to the intervention group and receive the rhPDGF-enhanced collagen intervention. The Standard Protocol Items: Recommendations for Interventional Trials (SPIRIT) schedule of enrollment, intervention, and assessments is included as Figure 1. A graphic study timeline of events is provided in Figure 2. The SPIRIT checklist is included in S1 Appendix. A full accounting of evaluations and unabridged protocol approved by the IRB is available in S2 Appendix (December 13, 2024; version 6.1) and important protocol modifications will be available from the corresponding author and by viewing the ClinicalTrials.gov (NCT06632418) study entry. A sample consent form is included in S3 Appendix.

### Setting

The trial will be conducted at Vanderbilt University Medical Center (VUMC) in Nashville, TN in the Department of Surgery, Division of General Surgery, section of Colon and Rectal Surgery.

### Recruitment and Consent

This study aims to recruit 12 participants, that are adults >21 years of age regardless of gender, race, or ethnicity. There is no information currently available regarding differential agent effects in participants defined by race or ethnicity. No vulnerable populations are expected to be enrolled in this study. The target number of patients to be screened for enrollment is 60 with the expectation of enrolling and randomizing ~25% of those screened and accounting for discontinuation, withdrawal, and loss to follow-up. This will be a single-site study at VUMC with an anticipated accrual rate of 1–2 participants per month.

Existing patients, new patients, and provider-referred patients with a diagnosis of a complex perianal fistula that is not amenable to a fistulotomy can be recruited for this trial. Patients that are interested in the trial will be scheduled for a screening visit where they will sign written informed consent and undergo the baseline examination for eligibility. Informed consent is initiated prior to the individual’s agreeing to participate in the study and continues throughout the individual’s study participation. Informed Consent Forms (ICF) will be VUMC Institutional Review Board (IRB)-approved. Only those participants who undergo the baseline procedure will be considered treated and count towards total participant population. Participants who signed consent but did not receive treatment will not be followed further.

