#### Screen Failures

Screen failures are defined as participants who consent to participate in the clinical trial but are not subsequently randomized or the device is unable to be implanted. A minimal set of screen failure information is required to ensure transparent reporting of screen failure participants, to meet the Consolidated Standards of Reporting Trials (CONSORT) publishing requirements and to respond to queries from regulatory authorities. Minimal information includes demography, screen failure details, eligibility criteria, and any serious adverse event (SAE).

Individuals who consent and do not meet the criteria for participation in this trial (screen failure) because of the following criteria may be rescreened once the below criteria have been resolved.

No draining seton in placeActive infectionSurgical procedures outlined in the exclusion criteriaParticipation in an investigational study as outlined in exclusion criteriaPregnant or breastfeeding

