### Randomization and Blinding

Randomization will occur at the baseline visit at a ratio of 2:1 intervention versus control. Randomization will be stratified to achieve balance in treatment allocation across idiopathic and CD-related fistula types. Because the total sample size is 12, randomization will be blocked using blocks of size 3 (2:1 intervention to control) within each stratum (idiopathic versus CD-related). Based on historical clinical data we anticipate enrolling 9 Chron’s participants and 3 idiopathic participants. Blinding of the patients, surgeons other than the investigator performing the procedure, and study team members assessing outcomes to study arm allocation will be employed to reduce bias in conducting study activities and evaluations. Given that the control group will be receiving a routine care procedure, the investigator who will be performing all procedures will be unblinded to the treatment assignment for each participant. To maintain blinding while assessing outcomes, clinical exams during follow-up study visits will be performed by another surgeon not involved in the initial screening visit or the procedural encounter. In the case of a serious adverse event or medical emergency in which knowledge of the treatment is necessary for the participant’s well-being or medical care, the unblinded investigator will be alerted to ensure appropriate medical management.

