### Administration

The following procedures will be performed by the surgeon for administration of the intervention.

A clinical examination under anesthesia with an anal fistula probe will be conducted to rule out active infection, anal stenosis, or active proctitis and confirm the presence of a single fistula tract.The seton will be removed, the fistula tract curetted vigorously to remove granulation tissue lining the tract, and the tract will be flushed with saline.The fistula tract length and diameter and amount of the sphincter muscle involved will be assessed by the surgeon with an anal fistula probe placed from the external to the internal opening.The appropriate model collagen matrix will be used based on the length of the tract.The collagen will be saturated with the rhPDGF solution in a sterile dish for a minimum of 10 min.After the collagen is fully saturated with rhPDGF, it will be pulled through the fistula tract carefully from the internal opening to the external opening.The collagen will be sutured to the rectal mucosa at the internal opening and any portion beyond the skin level will be trimmed to sit flush with the external opening.

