### Study Assessments and Procedures

#### Safety Assessments

Clinical examination
At screening, during the procedure, and at all follow-up visits, clinical examination of the perianal fistula will visually assess for infection, excess drainage, chronic inflammation, abnormal bleeding, or fibrosis at the external opening. Photographs of the external openings will be taken at screening and all follow-up visits to document healing progress.Patient medical history
At screening, patients meeting inclusion criteria will be screened for exclusion criteria through their medical history. The etiology of the perianal fistula will also be discussed and documented. Participants will review any known allergies, previous surgical procedures, previous complications, and frequency of fistula occurrence or recurrence.Pregnancy test
At screening, women of childbearing potential will be required to take a pregnancy test and must agree to use two reliable contraceptive methods for the duration of their participation in the study, one of which must be a barrier method; the contraceptive methods will be documented in the screening eCRFs.Crohn’s Concomitant Medications
At screening and all follow-up visits, Crohn’s medications will be documented for patients with CD-related perianal fistulas, including medication name, single dose amount, route, frequency, start date, and end date.Participant survey
At screening, baseline, and weekly following the procedure till Month 3, participants will complete a self-report questionnaire assessing the frequency and severity of pain, incontinence, and other perianal fistula-related symptoms. If symptoms are increasing in frequency and severity, an off-cycle clinical visit will be scheduled to address any adverse events.Assessment of adverse events
The following adverse events will be recorded in the eCRFs and followed until resolution:
Adverse events that are classified as related to study procedures (that is, potentially-, probably-, or definitely related to study procedures or of uncertain relationship to study procedures), regardless of severitySerious adverse events regardless of relatedness to study procedures.Clinical adverse events, events diagnosed as clinical conditions, with a severity grade ≥ 3, regardless of relatedness to study procedures.

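### The protocol conflicts on whether a randomized participant whose procedure was begun but whose implant could not be placed is treated, followed and analyzed, so the adverse-event comparison risks differential ascertainment by arm

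*Protocol article*

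**What the plan says.** All places are in the Protocol article.

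- **Recruitment and Consent** gives two adjacent rules: "Only those participants who undergo the baseline procedure will be considered treated and count towards total participant population", then "Participants who signed consent but did not receive treatment will not be followed further".
- **Screen Failures** defines the class as "participants who consent to participate in the clinical trial but are not subsequently randomized or the device is unable to be implanted". Only a minimal data set is required for it. That set lists serious adverse events but not non-serious ones.
- **Randomization and Blinding**: "Randomization will occur at the baseline visit at a ratio of 2:1 intervention versus control". The order of randomization and the examination under anesthesia is not given. For the strata, "we anticipate enrolling 9 Chron’s participants and 3 idiopathic participants".
- **Administration** starts with the examination under anesthesia and continues: "The seton will be removed, the fistula tract curetted vigorously to remove granulation tissue lining the tract". Pulling the collagen through and suturing it come last.
- **Safety Assessments**: "The following adverse events will be recorded in the eCRFs and followed until resolution". The list covers procedure-related events of any severity, all serious events, and clinical events of grade 3 or higher. It makes no exception for failed placement.
- **Efficacy Assessments** gives Crohn's controls seton removal and debridement without a device. Idiopathic controls also receive a commercial plug.
- **Secondary and Tertiary Outcomes Analysis** says that safety endpoints are analyzed for everyone randomized, as appropriate. Later, in the paragraph on Month 3 healing, it restricts the intervention arm to those who receive the intervention, because some exclusions can only be assessed at surgery. No matching restriction is stated for controls.

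**The concern.** A participant can be anesthetized, lose the seton and have the tract curetted before the surgeon finds that the collagen cannot be drawn through or secured. Under Screen Failures this person may become a screen failure, under Recruitment and Consent may leave follow-up, and under the modified intention-to-treat rule may leave the intervention arm. A Crohn's control who has had the same seton removal and debridement has completed the assigned treatment and is followed.

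Intervention-related adverse events within 3 months are a secondary safety outcome. The proportion with an event is compared between arms by Fisher's exact test, and counts per participant may be compared by a Mann-Whitney test. If the chance of having non-serious or later events recorded depends on arm, that comparison is not like for like. With 8 against 4 participants, a single person matters to the estimate.

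**Working it through.** **1. The rules applied to one participant: randomized to intervention, seton removed, tract curetted, implant not placed.**

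| Question | One reading | Other reading |
|---|---|---|
| Treated? | Yes: underwent the baseline procedure (Recruitment and Consent) | No: device not implanted, so a screen failure (Screen Failures) |
| Followed? | Yes: procedure-related events of any severity, to resolution (Safety Assessments) | Not assured: no follow-up without treatment (Recruitment and Consent); minimal data only (Screen Failures) |
| Analyzed for safety? | Yes: all randomized (Secondary and Tertiary Outcomes Analysis) | No: only recipients form the intervention arm (same section, modified intention-to-treat) |

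The second column cannot hold together with the first. Serious events are kept under both. Scheduled visits, weekly surveys, non-serious or later events, and a place in the denominator are not assured under the second.

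**2. Who can be affected.** Inputs: 9 Crohn's and 3 idiopathic participants expected, allocated 2:1 in blocks of 3.

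- Crohn's: 9 × 2/3 = 6 intervention, 3 control (no device).
- Idiopathic: 3 × 2/3 = 2 intervention, 1 control (plug).
- Able to have an unplaced device: 6 + 2 = 8 of 8 intervention; 1 of 4 controls.

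The imbalance lies in the Crohn's stratum. In the idiopathic stratum both arms have a device.

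**3. The plan's own figure.** The plan gives no rate of failed placement and no adverse-event rate. Its nearest figure, in Sample Size, is the lower Clopper-Pearson limit for 8 of 8 successes: 0.025^(1/8) = 0.631, which reproduces the stated 0.63. It assumes that all 8 succeed.

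**4. How likely one case is.** One failure is 1/8 = 12.5% of the arm. With an assumed failure rate p, P(at least one in 8) = 1 − (1 − p)^8:

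- p = 5%: 0.337
- p = 10%: 0.570
- p = 20%: 0.832

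**5. How far the intervention-arm proportion could move.** Let f be the failure rate, q the event rate after failed attempts and r the rate after completed ones. All attempts give fq + (1 − f)r and completed ones give r, so leaving out failed attempts understates the proportion by f(q − r). With r = 0.25 assumed:

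| f | q = 0 | q = 0.25 | q = 0.5 | q = 1 |
|---|---|---|---|---|
| 0.10 | −0.025 | 0 | 0.025 | 0.075 |
| 0.20 | −0.05 | 0 | 0.05 | 0.15 |

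**6. Single-case illustrations (assumed counts).**

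- If the failed case is replaced, so that 8 are implanted, and the failed case had an event: 0/8 (95% interval 0 to 0.37) should be 1/9 (0.003 to 0.48), and 1/8 (0.003 to 0.53) should be 2/9 (0.03 to 0.60). The shift is 10 to 11 points. Fisher's p against 0/4 is 1.0 throughout.
- If not replaced, with a true 4/8 against 1/4 (difference 25 points): omitting a failed case with an event gives 3/7 − 1/4 = 0.179, and omitting one without an event gives 4/7 − 1/4 = 0.321. The sign of the distortion depends on data that the plan does not give.

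**The case against.** A reader might infer that the protocol drops the harms of attempted implantation and so biases the comparison in favour of the intervention. The documents do not support that:

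- The no-follow-up sentence does not mention failed implants. The sentence before it counts anyone who undergoes the baseline procedure as treated. The no-follow-up reading depends on Screen Failures.
- The data set for screen failures is a minimum, not a ceiling, and includes serious events. Safety Assessments requires procedure-related events of any severity to be recorded, without exception.
- Bias, and its direction, need event rates after failed and completed attempts. The documents give neither. If the rates are equal, the bias is zero; if failed attempts have fewer events, the sign reverses.
- Inability to implant may mean ineligibility found at the examination, before curettage and possibly before randomization.
- The restriction to recipients stands in the paragraph on healing and need not govern safety.
- The article is condensed. The full protocol in its S2 Appendix, not shown here, may settle the matter.

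Most of this stands and limits the claim to a risk. It does not remove the conflict. The device clause in the screen-failure definition is separate from non-randomization, so it can reach randomized participants. An attempt to place the study collagen can only follow allocation to it, and by the Administration sequence it follows seton removal and curettage. For that participant the article's stated rules give opposite answers.

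**Conclusion.** The concern holds as a conflict between stated rules that creates a risk of differential ascertainment of adverse events. All 8 intervention participants and the 1 expected idiopathic control could be reclassified after surgery has begun; the 3 expected Crohn's controls could not. This rests on the anticipated 9:3 split and on reading Recruitment and Consent, Screen Failures and the modified intention-to-treat rule together.

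The size is unknown. Under the assumed rates above, the change in the intervention-arm proportion runs from nothing to several points in expectation, and about 10 points for one omitted case with an event. Test conclusions would hardly change at this sample size, but the plan puts confidence intervals before p-values and summarizes safety descriptively, so the estimates matter. The point should be corrected; it does not show that the safety result will be wrong.

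**What to change.** - In Recruitment and Consent and in Screen Failures, limit the no-follow-up rule and the screen-failure class to participants who were not randomized or whose baseline procedure was never begun.
- State that every randomized participant whose procedure was begun (anesthesia, seton removal or curettage) stays under the same adverse-event ascertainment to Month 3 as all others, whether or not an implant was placed.
- In Secondary and Tertiary Outcomes Analysis, state that these participants are counted by randomized arm in all harm tables and tests.
- Reconcile these sections with Safety Assessments, and state when randomization takes place relative to the examination under anesthesia.

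This concerns data collection and analysis only and implies no rule for clinical care after an unplaced implant. The cost is protocol wording, existing visits for perhaps one or two participants, and intervention-arm figures that may look slightly less favourable.
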